### Main outcomes of the intervention

The main outcome variables are AOD use and sexual risk behavior at 3-, 6-, and 12-month follow-up. Using items based on the Monitoring the Future survey [82], we will assess the number of days, in the past 30 days, participants engaged in the use of various substances, including alcohol use, heavy alcohol use, cannabis use, non-medical prescription drug use, and use of several types of illicit drugs (e.g., heroin, methamphetamine, hallucinogens). Information is also collected on the quantity of alcohol use (drinks per day) and marijuana use (times per day) on the days these substances are used. We are administering the Global Appraisal of Individual Needs–Short Screener (GAIN-SS) [83] to explore whether intervention effects on AOD outcomes might be weaker for those with a high probability of a past year substance use disorder (scores of 3 or greater), compared to those with a low-moderate probability of a disorder. In addition, we assess the importance of cutting down or stopping their alcohol, marijuana, and other drug use (or, if they do not currently use, the importance of remaining a non-user) with separate motivation to change rulers for each type of substance (0 = *not at all important* to 10 = *extremely important*) [84]. We are assessing sexual risk behavior using both past 90 day and past 30 day timeframes, with the main outcome being the proportion of unprotected sexual events. In addition, we are assessing condom use self-efficacy using the Self-Efficacy Instrument for Protective Sexual Behaviors [85].

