### Analytic plan

We will compare the intervention and control groups on each of the primary and secondary outcomes with a multilevel modeling approach using SAS PROC MIXED for continuous outcomes (e.g., past month quantity-frequency of alcohol use; proportion of protected sex acts; past month income) and PROC GLIMMIX for categorical or count outcomes with overdispersion and/or zero-inflation accounted for as needed in the modeling approach (e.g., any past month heavy drinking; number of sex partners; number of jobs in past 3 months) using restricted maximum likelihood estimation. Outcomes will be tested at each time point (3-, 6-, and 12-months) and longitudinal analyses will be used to test for differences in change over the 12-month period. Although testing at each time point provides estimates of the intervention effect at that time, the longitudinal analysis will capture patterns of change over time, that is, whether the average change on outcomes within each group produce parallel lines over time vs. lines with different slopes vs. non-linear patterns. We will explore dose–response relationships given that participants voluntarily choose to attend 1 to 4 program sessions. Although we consider any attendance as receiving the intervention, attending more sessions may be associated with better outcomes [86]. In addition, we will conduct an analysis to explore whether observed program effects differ by gender or substance use severity (defined by a score of 3 or higher on the GAIN-SS) [83] by estimating separate models for each group and/or by including an interaction term in the models.

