## Limitations and alternative methods considered

The AWARE curriculum does not include specific references to marijuana (although it is discussed if a participant brings it up during a session), due to focus group feedback indicating that these young adults are not interested in attending a program that addresses their marijuana use. Nonetheless, our pilot work found positive intervention effects on motivation to change marijuana use among lower severity users [1], and we plan to examine intervention effects on marijuana use and related attitudes in this larger evaluation. The study is also limited by its exclusively reliance on self-report data, although this is typical for most research of this nature. Finally, although the evaluation is being conducted in agencies located in two distinct areas of Los Angeles County, it is unclear whether results will generalize to other agencies located in other geographic regions.

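### Several AOD measures and unprotected sex in two recall windows are all main outcomes, tested at three visits and longitudinally, with no measure, window, visit or test fixed as decisive

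*Protocol article*

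**What the plan says.** Under Main outcomes of the intervention: "The main outcome variables are AOD use and sexual risk behavior at 3-, 6-, and 12-month follow-up". The same paragraph lists past-30-day days of use, "including alcohol use, heavy alcohol use, cannabis use, non-medical prescription drug use, and use of several types of illicit drugs (e.g., heroin, methamphetamine, hallucinogens"), and continues: "Information is also collected on the quantity of alcohol use (drinks per day) and marijuana use (times per day"). Sexual risk is assessed "using both past 90 day and past 30 day timeframes, with the main outcome being the proportion of unprotected sexual events".

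The second Analytic plan section compares the arms on every primary and secondary outcome, and states: "Outcomes will be tested at each time point (3-, 6-, and 12-months) and longitudinal analyses will be used to test for differences in change". Its examples of modelled outcomes include a quantity-frequency measure of alcohol and "any past month heavy drinking; number of sex partners; number of jobs in past 3 months", so further forms of the same behaviours appear there.

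The present study section gives the primary aim as reductions in AOD use and sexual risk over a 12-month period. The limitations section says: "The AWARE curriculum does not include specific references to marijuana". It adds that marijuana is discussed if a participant raises it and that effects on its use will be examined.

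**The concern.** Which variable, visit and comparison decide success belongs in the protocol. Here a section on main outcomes declares a whole family of measures at three visits, and the analysis section gives each outcome three visit tests and a longitudinal one. Nothing ranks them. A reader of the final report could not tell from the protocol whether success means fewer drinking days at 3 months, less methamphetamine use at 6 months, a different 12-month trajectory of heavy drinking, or less unprotected sex over 30 rather than 90 days.

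If each test is read on its own, one favourable result among many could be presented as a positive primary finding. The pilot shows why this matters. It found significant alcohol effects but none on drug use. It found no significant effect on unprotected sex in the full sample, but one in a subsample with multiple partners (p = .04).

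**Working it through.** The article gives no alpha, power or family-wise error for the outcome tests, so there is no stated figure to reproduce. I counted the tests and computed the error rate.

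**Count of measures** (Main outcomes of the intervention)
- Days of use: alcohol, heavy alcohol, cannabis, non-medical prescription drugs, plus the three illicit drugs named as examples = 7.
- Quantities: alcohol and marijuana = 2. AOD upper count: 7 + 2 = 9.
- AOD lower count: pool the illicit drugs and merge alcohol days with drinks per day. That leaves alcohol quantity-frequency, heavy alcohol, cannabis days, marijuana quantity, prescription drugs and illicit drugs = 6.
- Unprotected sex: 1 measure, or 2 if the recall windows count separately.

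I carried two counts forward: **8** (7 day-counts + 1 sexual measure) and **11** (9 AOD + 2 windows).

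**Count of tests** (second Analytic plan section)
- Visit tests only: 8 × 3 = 24; 11 × 3 = 33.
- With the longitudinal test: 8 × 4 = 32; 11 × 4 = 44.

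**Chance of at least one false positive if AWARE has no effect.** Assumed: two-sided 0.05 per test, unadjusted. For m independent tests it is 1 − 0.95^m; counting only results favouring AWARE it is 1 − 0.975^m. For correlated tests I used normal test statistics with one common pairwise correlation ρ. The documents give no correlations, so ρ is a range.

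| Tests | ρ = 0 | ρ = 0.5 | ρ = 0.7 |
|---|---|---|---|
| 24 (8 × 3) | 1 − 0.95^24 = 71% | 46% | 31% |
| 32 (8 × 4) | 1 − 0.95^32 = 81% | 52% | 35% |
| 33 (11 × 3) | 1 − 0.95^33 = 82% | 53% | 35% |
| 44 (11 × 4) | 1 − 0.95^44 = 90% | 59% | 39% |

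Favouring AWARE only:

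| Tests | ρ = 0 | ρ = 0.5 | ρ = 0.7 |
|---|---|---|---|
| 24 | 46% | 23% | 16% |
| 32 | 56% | 26% | 17% |
| 33 | 57% | 27% | 18% |
| 44 | 67% | 30% | 19% |

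**Sensitivity to the correlation structure.** The longitudinal test uses the same visit data, so treating it as independent overstates the 44-test figure. I therefore also simulated 11 measures with separate correlations between outcomes (0 to 0.7) and between visits (0.3 to 0.7), with the fourth test as a slope over the three visits. Over 44 tests this gave 52–86% in either direction and 29–63% favouring AWARE. At 0.5 for both correlations the figures were 69% and 41%.

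**For comparison.** One measure at one visit gives 5%. Two primaries, each at unadjusted 0.05 and independent, give 1 − 0.95² = 9.75%. Two primaries under Holm give at most 5% whatever their correlation.

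**The case against.** The strongest reply is that a condensed article may leave multiplicity control to an analysis plan that is not shown, and that the unadjusted 0.05 is the reviewer's assumption. That stands. A missing alpha or adjustment rule is not the finding, and the percentages are conditional. What remains is what the article does state: a family of main outcomes at three visits, each tested several ways, with none decisive.

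Four stronger readings are tempting but not supported.

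- **That no primary measure exists at all.** For sexual risk the proportion of unprotected sexual events is named as the main outcome. The open items there are window, visit and test; only in the AOD domain is the measure itself open.
- **That the plan departs from a month-12 aim.** The aim is change over 12 months, and the longitudinal analysis answers it. The difficulty is that this analysis is not given precedence over the visit tests.
- **That at least 11 behaviours will be tested.** Eleven counts quantities and recall windows separately, and takes three illicit drugs given only as examples. Alcohol days and drinks per day may be merged. The 8-measure figures are there for this reason.
- **That including cannabis is an error.** The article discloses that marijuana has no specific curriculum content, allows its discussion, and gives a reason for examining it: pilot effects on motivation to change among lower-severity users. Its rank is a matter of judgement.

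Nor can one say that a chance positive is always more likely than not. At ρ = 0.7 the chance is 31–39%, and for results favouring AWARE much of the range lies below half.

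**Conclusion.** The concern holds in this form: the protocol does not fix which AOD measure, which recall window for unprotected sex, which visit, or which of the visit-wise and longitudinal tests decides success. With an assumed unadjusted two-sided 0.05, the chance of at least one false positive among the main outcomes is about 31–81% for 8 measures and 35–90% for 11. Counted only in favour of AWARE it is about 16–67%. The spread reflects unknown correlations and how the measures are counted. Even the lowest two-sided figure is about six times 5%, and the lowest figure favouring AWARE is about six times the 2.5% that a single test would give in that direction. The conclusion does not depend on the exact percentage: the deciding comparison is left open under any count.

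**What to change.** Before the arms are compared:

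1. Name one primary AOD measure.
2. Name one recall window for the proportion of unprotected sexual events.
3. Name one deciding test for both: either the longitudinal group difference over 12 months, which matches the stated aim, or the 12-month contrast.
4. Test the two primaries with Holm at an overall 0.05.
5. Make the remaining measures, visits and tests secondary, with false-discovery-rate control. Cannabis would fall here unless chosen as the AOD primary.

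If the AOD primary is chosen on pilot evidence, note that the pilot signals were past-3-month alcohol frequency (d = 0.31) and frequent-heavy drinking (d = 0.22). No pilot result is reported for past-30-day days of alcohol use. The full pilot sample showed no significant effect on unprotected sex.

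**Cost.** A change of wording, with no new data. The smaller p-value is compared with 0.025, and the larger with 0.05 only if the first passes. As a rough guide, take 200 per arm, d = 0.31, and no clustering or dropout. The expected z is 0.31 × √(200/2) = 3.1. Power is then Φ(3.1 − 1.96) = 87% at 0.05 and Φ(3.1 − 2.24) = about 80% at 0.025. A Bonferroni correction over all 44 tests (0.05/44 = 0.0011) would leave about 44%, which is why choosing two primaries is better than adjusting for the whole set.

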## Brief, yet effective AOD and sexual risk reduction programs for young people experiencing homelessness are needed [34]

To date, brief interventions for these young people have tended to focus solely on AOD or HIV/STD prevention alone (i.e., they have not targeted the unique combined risks from both AOD use and risky sex behaviors evident among this population, such as impaired decisions to have condomless sex following heavy drinking or drug use), and have demonstrated minimal long-term efficacy. One study evaluated a single-session one-on-one Motivational Interviewing (MI) intervention, which presented youth with personalized feedback about their patterns of risk associated with AOD use [35]. The intervention group showed reduced illicit drug use other than cannabis at 1-month follow-up compared to the control group; however, this effect was not sustained by 3-month follow-up, and no effects were found on alcohol or cannabis use. Another study evaluated a similar type of one-on-one motivational intervention, but delivered over four sessions with an average total treatment exposure of 73 min [36]. The program did not have a statistically significant effect on AOD use at 3-month follow-up. Other brief interventions include a street outreach HIV prevention intervention that offered service listings/referrals and supplies (e.g., condoms and bleach), which did not find a statistically significant effect on condom use [37], and a peer-delivered HIV prevention intervention, which did not significantly reduce AOD use or sexual risk behavior at 3-month follow-up [38]. Finally, a 2-session HIV intervention for homeless youth receiving substance use treatment through a drop-in center had a statistically significant effect on condom use at 6-month follow-up, but this effect dissipated by 12 months [39]. Although this research has demonstrated the feasibility of implementing risk reduction interventions with homeless youth, very brief motivational interventions have not demonstrated long-term efficacy compared to standard care, which typically consists of case management, basic services (food, clothing), and other programs to meet the therapeutic, health, and other needs of homeless youth. A review of risk reduction interventions for runaway youth and those experiencing homelessness concluded that programs need to be intensive enough to address the multiple and interrelated risk behaviors that most homeless adolescents and young adults exhibit, yet practical to deliver in the busy service settings where these young people routinely seek services [40]. Of course, youth with a substance use disorder may need more intensive treatment than a brief intervention is designed to provide.

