### Analytic plan

Baseline data will be collected from participants using self-administered paper–pencil surveys, with the survey response forms then scanned and checked for accuracy. Follow-up data will primarily be collected using either scannable paper–pencil surveys or a web-based version of the survey. Participants who cannot complete a follow-up survey in one of these ways will be offered the option of completing the survey by phone (we expect these cases to be rare). Preliminary analyses will be conducted to: (a) examine the distribution of items and correct where necessary using, for example, a log transformation for skewed outcomes and/or centering of items as appropriate; and (b) determine whether the intervention and control groups differ on baseline characteristics (t-tests and Chi square tests). Observed differences at *p* < 0.20 may be subsequently controlled for in analyses testing intervention effects. All analyses will be intention to treat–that is, we will analyze people in the groups to which they were assigned, regardless of their attendance at the sessions. In terms of missing data and attrition, our general modeling approach will allow for the inclusion of all study participants who completed the baseline survey. We will explore patterns of missingness and use logistic regression models to gain a better understanding of the baseline predictors of study drop out (i.e., non-completion of the 3-, 6-, and 12-month assessments). To accommodate missingness in analyses we will use either an inverse probability weighting approach or multiple imputation [81].

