We initially considered a design in which individuals would be randomly assigned to condition within agency. However, we decided against this design given concerns on the part of the research team and drop-in center staff about implementation challenges (e.g., clients perceiving that they were being refused services that other clients were getting) and the strong potential for contamination across conditions. A group-randomized design was a much better option for this evaluation in that it addressed these concerns. We are maximizing the comparability of the intervention and control groups by having each drop-in center serve as both intervention and control site on an alternating basis, as well as using the same procedures at each drop-in center to identify and recruit participants for the study. In addition, once data are collected, we will conduct preliminary analyses to determine whether the intervention and control groups differ on baseline characteristics. This step is necessary despite randomization as randomization is not occurring at the individual level. In the pilot evaluation, which used the same procedure, there were no significant baseline group differences on demographic characteristics. However, any observed differences will be controlled for in all analyses testing intervention effects with the addition of model covariates. If we observe considerable differences in the intervention and control groups that cannot be adequately accounted for with the addition of model covariates, we will develop analytic weights using propensity methods to balance the groups. We will also control for any within-agency effects by including agency as a fixed effect (dummy coded) within the models.

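### Adjustment for each outcome's baseline value is left to an imbalance screen worded in two conflicting ways, when it could be built into every outcome model at no cost

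*Protocol article*

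**What the plan says.** Three places in the protocol article bear on this.

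- **First Analytic plan section (data collection and preliminary analyses).** The arms are compared on baseline characteristics with t-tests and chi-square tests. Differences at p < 0.20 "may be subsequently controlled for in analyses testing intervention effects". This is optional and has a threshold.
- **Limitations and alternative methods considered.** Here "any observed differences will be controlled for in all analyses testing intervention effects with the addition of model covariates". This is mandatory and has no threshold. Propensity weights are held in reserve for differences that covariates cannot handle. Agency enters as a dummy-coded fixed effect and is the only covariate included whatever the data show. The same paragraph says that the baseline check is needed because randomization is not at the individual level.
- **Second Analytic plan section (multilevel models).** The tests are set out as follows: "Outcomes will be tested at each time point (3-, 6-, and 12-months) and longitudinal analyses will be used to test for differences in change". Change is judged up to month 12, and the longitudinal part asks "whether the average change on outcomes within each group produce parallel lines over time vs. lines with different slopes vs. non-linear patterns". No baseline-outcome covariate is named for the visit tests. The section does not say whether baseline is a time point in the longitudinal model, or whether time is linear or categorical.

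Every participant completes a baseline survey before the intervention (Procedures), so the baseline values are already being collected.

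**The concern.** A baseline value is worth adjusting for because it predicts the follow-up value. Whether it happens to differ between arms says little about that. If adjustment is triggered by a test at p < 0.20 and the arms are comparable in expectation, about one trial in five adjusts for a given outcome. The other four in five discard the information.

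The two sentences also give different analyses for the same data. With a baseline difference at p = 0.10, one permits adjustment and the other requires it. With a difference at p = 0.40, the first does not call for adjustment, while the second does if *any observed* is read literally. The analyst would choose after seeing the data.

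The design raises the stakes a little. Three drop-in centers alternate condition by recruitment cycle, so arms can differ at baseline for reasons that individual randomization would have averaged out. Routine adjustment for the baseline outcome guards against this; a significance screen does so only when the difference passes the threshold.

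**Working it through.** **No stated figure to reproduce.** The article gives 200 per arm but no alpha, power, design effect size or baseline correlation.

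**Inputs.** From the article: 200 per arm. Assumed: two-sided alpha 0.05, d = 0.25, baseline-to-follow-up correlation ρ of 0.3, 0.5 or 0.7, a continuous outcome, no clustering and no attrition. It is also assumed that the screen covers the outcome's own baseline value and is always acted on, which is generous to the stated rule.

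**Step 1: unadjusted.** The expected test statistic is d × √(n/2) = 0.25 × √100 = 2.50. Power is 70%.

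**Step 2: always adjusted.** The residual SD falls to √(1 − ρ²), so the expected statistic is 2.50/√(1 − ρ²).

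**Step 3: p < 0.20 screen.** Let z_b be the standardized baseline difference, with mean zero. The unadjusted statistic is z_y = 2.50 + ρ·z_b + √(1 − ρ²)·e. The adjusted one is (z_y − ρ·z_b)/√(1 − ρ²). Use the adjusted statistic if |z_b| > 1.28 (p < 0.20) and z_y otherwise. Simulation shows adjustment in about 20% of trials.

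| ρ | Expected statistic, always adjusted | Unadjusted | p < 0.20 screen | Always adjusted |
|---|---|---|---|---|
| 0.3 | 2.50/0.954 = 2.62 | 70% | 72% | 74% |
| 0.5 | 2.50/0.866 = 2.89 | 70% | 74% | 82% |
| 0.7 | 2.50/0.714 = 3.50 | 70% | 78% | 94% |

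Against the stated screen, the gain is about 2, 8 or 16 points.

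**Step 4: other inputs.** Take the pilot's alcohol-frequency effect (d = 0.31) and its 91% follow-up rate (200 × 0.91 = 182 per arm). Power is 84.1% unadjusted. The screen gives 85.1%, 87.0% or 90.2%, and routine adjustment gives 87.3%, 92.7% or 98.5%, at the same three correlations. The gain over the screen is about 2, 6 or 8 points.

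**Step 5: linear slope against visit contrasts.** Use visits at 0, 3, 6 and 12 months, 200 per arm and a common correlation of 0.5. The mean time is 5.25, the deviations are −5.25, −2.25, 0.75 and 6.75, and their squares sum to 78.75. The standard error of the slope difference is √(0.5 × 2/200 ÷ 78.75) = 0.00797 per month.

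- Effect that half fades (0, 0.3, 0.225, 0.15): slope (−0.675 + 0.169 + 1.013)/78.75 = 0.0064, z = 0.81, power 13%. The baseline-adjusted average of the three follow-ups is 0.225, with standard error √[((1 + 2 × 0.5)/3 − 0.25) × 0.01] = 0.0645 and power 94%.
- Effect that is held (0, 0.3, 0.3, 0.3): slope 1.575/78.75 = 0.020, z = 2.51, power 71%. The adjusted average has over 99%.
- Effect gone by 12 months (0, 0.3, 0.3, 0): slope −0.45/78.75 = −0.0057, z = −0.72, rejection 11%. In this same case a three-degree-of-freedom group-by-time test with categorical time has 96% power, and even the unadjusted 3-month test has 85%.

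**The case against.** The strongest reply is that a condensed article need not list the covariates of each model. Nothing says that the baseline outcome is left out, and an analysis of change over 12 months may well contain baseline as a time point. That stands against any claim that the comparisons are unadjusted. A reader might infer that from the second Analytic plan section, but the Limitations section requires adjustment for observed differences. It does not answer the narrower point: the article does state a rule for covariates, in two versions that conflict, and both make adjustment depend on observed imbalance.

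A reader might also infer that the longitudinal test would miss or reverse a true early benefit. The Background encourages this, since it cites a two-session HIV program that "had a statistically significant effect on condom use at 6-month follow-up, but this effect dissipated by 12 months". The article does not support it:

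- The longitudinal sentence expressly includes non-linear patterns.
- The plan says that "testing at each time point provides estimates of the intervention effect at that time", so an early effect would be seen at 3 or 6 months.
- No sentence makes a linear slope the deciding test.
- With baseline in the model, the slope takes the wrong sign only after nearly complete fading. For effects 0, 0.3, 0.3, x the sign turns where −0.675 + 0.225 + 6.75x = 0, so x = 0.067, or 22% of the effect.
- The cited program is a different one, and the article predicts no such course for AWARE.

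Finally, the power figures use assumed effects and correlations, and the variance formula applies to continuous outcomes; it does not carry over directly to the categorical, count or zero-inflated ones. This is fair, and it limits the size claimed more than the direction.

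**Conclusion.** The point holds as a free improvement, not as an error that would invalidate the trial. Adjustment for the baseline outcome rests on an imbalance screen that is optional with a threshold in one section and mandatory without one in another. Replacing it with unconditional adjustment gains about 2, 8 or 16 points of power at a single visit over the p < 0.20 screen, at assumed correlations of 0.3, 0.5 or 0.7 with d = 0.25 and 200 per arm. All the power levels ignore clustering by site and cycle, and the d = 0.25 figures also ignore attrition, so they are upper limits. The gain is small if the correlation is low. Routine adjustment also gives steadier protection against baseline differences in a design without individual randomization; that benefit is not quantified here.

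On the longitudinal analysis, the conclusion is limited to this: a linear slope difference is a weak summary of an early effect that partly fades, and categorical time avoids the problem. The visit-specific tests already planned would show such an effect.

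**What to change.** 1. Include the baseline value of the outcome as a covariate in every outcome model, together with agency, regardless of observed imbalance. Alternatively, fit one repeated-measures model per outcome with time categorical (0, 3, 6 and 12 months) and a common baseline mean across arms.
2. Report adjusted contrasts at 3, 6 and 12 months. In the longitudinal analysis, treat time as categorical and do not rely on a linear slope difference.
3. Replace the two conflicting sentences, in the first Analytic plan section and in Limitations and alternative methods considered, with one rule that matches. Baseline comparisons can stay as description, and propensity weighting can stay as the stated fallback.

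The cost is a change of wording and model code. No new data, visits or participants are needed. It should be made before outcome data are compared by arm.
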